## **A multicenter clinical trial (phase III) to evaluate the efficacy and safety of hemoporphin for injection for the treatment of port-wine stains**

### **1. Trial background**

Port-wine stains, also known as nevus flammeus or nevus telangiectasia, can occur in any part of the body, more frequently in the face, neck and scalp, affecting the appearance and psychology of patients. Port-wine stains is malformation of the superficial dermal capillaries, the essential difficulty in treatment is to remove the dilated superficial dermal capillaries to eliminate the abnormal red color of the lesion area without damaging the epidermis and deep dermal tissues in order to achieve a scar-free therapeutic goal. Treatments including cryosurgery, excision followed by skin grafting, X-ray, isotope and laser either leaves scars or is unable to eliminate color of the lesion area completely. Therefore, it is a clinical challenge to develop highly selective therapeutic methods.

Photodynamic therapy (PDT) is a therapeutic method that employs photosensitizers to generate cytotoxic substances after irradiation with visible light of specific wavelengths to act on the target tissues and produce histological effect. The photosensitizers can absorb photons and pass the energy to oxygen molecules to induce chemical reactions producing singlet oxygen and other toxic substances. An important property of photosensitizers is the ability to concentrate preferentially in the lesional tissues to produce specific biological effects with minimal impact on the surrounding normal tissues. Currently, PDT has demonstrated remarkable efficacy in the treatment of condyloma acuminata, actinic keratosis and other diseases.

The mechanism of PDT for the treatment of port-wine stains: because the photosensitizer obtains a plasma concentration peak immediately after its intravenous injection followed by rapid absorption by the vascular endothelial cells with little absorption in the epidermal cells, the distribution of injected photosensitizer forms an apparent concentration gradient between the vascular endothelial cells and the epidermal cells. Then transepidermal laser irradiation using specific wavelengths of selective absorption can activate the photosensitizers to generate singlet oxygen and other phototoxic substances, leading to selective destruction of the dilated and malformed capillary networks containing abundant photosensitizers at the lesion site without damaging the top normal epidermis containing little photosensitizers, the underneath dermal tissues are also protected because the limited laser penetration.

Photosensitizer is one of the key factors of PDT efficacy. Despite the significant results achieved with clinical application of the first generation of photosensitizers (hematoporphyrin derivatives, HpD), the skin phototoxicity reaction still lasts for 1~2 months and up to 3~4 months in some patients because HpD is a mixture of multiple porphyrins with strong affinity with collagen fibers,

its composition and chemical structure are yet to be clarified fully, and its excretion from the body is fairly slow. The patients must be strictly protected from light during this period, which severely affect not only the patient's quality of life and work but also cause great inconvenience in clinical treatment. Therefore, the current issue to be addressed urgently in order to meet the clinical demands on PDT is to develop photosensitizers with single chemical composition, clear structure, stable physicochemical properties, ideal action spectrum, high target tissue selectivity, strong photodynamic effect, low toxicity, and rapid metabolism.

Hemoporphin (hematoporphyrin monomethyl ether, HMME or MHD in short) co-developed by Shanghai Fudan-Zhangjiang Bio-Pharmaceutical Co., Ltd. and Chinese PLA General Hospital is a new drug for monomeric porphyrin photodynamic therapy. HMME methanol solution has characteristic absorption peaks at 401, 500, 533, 569 and 613 nm. HMME can be cleared from the tissues rapidly with very low phototoxicity in normal tissues. Both the acute toxicity and long-term toxicity of this compound are lower than the first-generation photosensitizers hematoporphyrin derivatives. The clear structure and rapid metabolism lead to mild adverse reactions, short period of protection from light, and treatments might be repeated within short intervals.

Based on the requirements of the drug clinical study approval notice number 2005L01082 issued by State Food and Drug Administration (SFDA), hemoporphin for injection phase III clinical trial is led by Peking University First Hospital and participated by Institute of Dermatology of Chinese Academy of Medical Sciences, The Ninth People's Hospital of Shanghai Jiaotong University School of Medicine, Guangzhou General Hospital of Guangzhou Military Region, Huashan Hospital of Fudan University, Xijing Hospital of the Fourth Military Medical University, Union Hospital of Tongji Medical College, Huazhong University of Science and Technology, and Xiangya Hospital of Central South University. The study purpose is to evaluate the efficacy and safety of hemoporphin for injection co-developed by Shanghai Fudan-Zhangjiang Bio-Pharmaceutical Co., Ltd. and Chinese PLA General Hospital for the treatment of port-wine stains using PDT method.

Based on the phase II clinical trial results showing that 5mg/kg hemoporphin and photodynamic irradiation for 20min were safe and effective in the treatment of port-wine stains, the phase III clinical study is to further verify the efficacy and safety of PDT using hemoporphin for port-wine stains.

## 2. Trial purpose

This study is to evaluate the efficacy and safety of hemoporphin for injection for the treatment of port-wine stains using placebo as the control in two stages of PDT treatments. Primary endpoint will be established at the first stage, and safety analysis will include both stages.

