## 3. Trial design

### 3.1 Design principle:

This is a parallel, placebo-controlled, double-blinded and multicenter clinical trial.

The subjects are randomized into trial group and control group at 3:1 ratio in this phase III clinical trial.

Statistical estimation of the sample size: using two-sided test of the efficacy,  $\alpha=0.05$  and  $\beta=0.1$  (power=90%) based on phase II clinical trial results, the expert panel estimates the total clinical efficacy rate of hemoporphin for injection to be 75.0% in the treatment of port-wine stains and expects a 40% difference from the placebo group; consequently, the estimated minimal number of subjects is 66 for the trial group and 22 for the control group.

In compliance with the SFDA requirement of minimum sample size of no less than 300 subjects for phase III clinical trial group, and also taking into account of dropout, the sample size of this clinical trial was determined to be 330 subjects for the trial group and 110 subjects for the control group, giving a total of 440 subjects.

The subjects will be assigned into trial group or control group by stratified block randomization to receive not more than 2 courses of treatment. The control group receive placebo during the first course of treatment followed by trial drug during the second course of treatment. Each course of treatment will last for 8 weeks. Based on the phase II clinical trial results, the trial drug dose is set at 5mg/kg.

The trial design profile is shown in the following table.

| Trial period                   | Hemoporphin for injection dose | Group and number of cases     | Design principle                                                          |
|--------------------------------|--------------------------------|-------------------------------|---------------------------------------------------------------------------|
| The first course of treatment  | 5mg/kg                         | 330 subjects in trial group   | Randomized, double-blinded, placebo and parallel-controlled (multicenter) |
|                                | 0mg/kg                         | 110 subjects in control group |                                                                           |
| The Second course of treatment | 5mg/kg                         | 330 subjects in trial group   | Randomized, double-blinded (multicenter)                                  |

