- 5) Precautions: the patients should be instructed to observe the photoreaction after drug infusion and pay attention to photo protection. The photoreaction is expected to disappear completely in approximately 10 days after drug infusion. During the light protection period (2 weeks), the subjects should pay attention to protection of the exposed skin and eyes, avoid irradiation of sunlight or strong indoor lights. In case of drug extravasation during the infusion, the extravasation area must be kept completely away from light for a fairly long time until local swelling and discoloration disappears completely, otherwise severe local skin photoinjury may occur.
- 6) PDT may cause the following treatment reactions: the patients may experience itching, burning sensation, pain, swelling, blisters and scabs at the irradiated and surrounding area. These therapeutic responses are usually transient and self-healing without special treatment.
- 7) Adverse reactions: If light protection measures are not taken properly, some patients may experience photosensitive reactions such as photosensitive dermatitis, photosensitive ophthalmia, photosensitive cheilitis, etc; some patients may experience nausea, dizziness, headache, drowsiness, total bilirubin elevation, hyperpigmentation, hypopigmentation,

treatment site infection, scarring and other adverse reactions.

- 8) At week 8 after the first treatment, if the color of treatment area has not subsided completely and there are no serious pigmentation, scarring and other conditions that are unsuitable for re-treatment according to the investigator's judgment, the next stage treatment can be carried out.

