#### 4.4 Drug packaging and blinding

Because the drug used in this trial is powder for injection and the doses for the control group and trial group are different, stimulant is inappropriate for the double-blinded design; considering the fact that the trial drugs are prepared by nurses, the sponsor will prepare the drugs for each group per the double-blinded requirement during the drug preparation period.

Identical drug outer packaging are used for both groups; each patient needs an independent large packaging that contains two medium packaging marked with "drugs for the first course of treatment or drugs for the second course of treatment". Each medium packaging includes drugs for trial group (5 bottles of drugs in each medium packaging) and control group (each medium packaging contains 5 empty bottles for the first course of treatment and 5 bottles of drugs for the second course of treatment).

The statisticians will provide the random number table generated using DAS software simulation and provide it for random blinding of the drugs. Stratified block randomization is carried out by trial centers. Drug coding is completed by personnel unrelated to this clinical trial.

During the trial period, each center assigns a special person to manage the trial drugs and a nurses will prepare the trial drugs, keeping the investigators and subjects blinded.

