### 14.1 Primary Populations

The primary efficacy variable will be summarized and analyzed in ITT and PP populations, the secondary efficacy variables will be summarized and analyzed in ITT populations. ITT population will be the primary analysis population.

✧ Full analysis set (FAS): refers to the set of eligible cases and dropout cases excluding the

rejected cases. The ITT population will be defined as all randomised patients having received at least one dose of either the tested or the reference treatments.

- ✧ Per protocol set (PPS): The PP population will be defined as all the subjects who completed the treatment period without any major deviation from the protocol.
- ✧ Safety set (SS): Safety population will be defined as all the subjects who received at least one treatment and have actual data of safety indexes.

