#### 14.5 Contents of statistical analysis

1. Case distribution: provide the sizes of different data sets of all groups, distribution of the cases among all centers, comparison of the total dropout rate, and a detailed listing of the reasons for termination.
2. Comparability analysis: demographic data and other baseline indexes are compared to measure the intergroup comparability.
3. Compliance analysis: (1) Drug compliance analysis: compare whether the patients of the two groups have taken the correct doses of trial drugs in timely manner without using the prohibited drugs and food as described in this protocol. (2) Drug combination analysis: count the number of subjects receiving drug combination in each group and provide a detailed list.
4. Efficacy analysis: PP and ITT analysis of the primary efficacy should be carried out at the same time; because this study is a multicenter clinical trial, the impact of center effect on the efficacy should be considered during analysis.
5. Analysis of the efficacy influencing factors: if there are significant differences in age, gender, disease types, disease conditions and other factors between the two groups before drug treatment or relevant factors significantly affecting the efficacy (e.g. drug combination) during the trial process, these factors should be used as covariates for analysis of covariance or logistic regression analysis during intergroup efficacy comparison.
6. Safety analysis: based on the requirements for correlation of adverse reactions, use listings to describe the AEs and adverse reactions in both groups (including the number of cases of various

AEs, the number of cases with "normal shift to abnormal" or "exacerbation of the abnormality" of the laboratory test indexes and abnormal conversion rate before and after this trial), list the causes and explain. Chi-square test is used for statistical analysis of the adverse reactions.

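### Sections 2 and 14.5(6) together set a between-group safety comparison with no split by course, although controls who enter course 2 receive hemoporphin

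*Protocol*

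**What the plan says.** The scope is set in section 2: "Primary endpoint will be established at the first stage, and safety analysis will include both stages".

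The control group's treatment is set in section 3.1: "The control group receive placebo during the first course of treatment followed by trial drug during the second course of treatment". The design table there gives 5 mg/kg to both groups in the second course. The control packaging in section 4.4 agrees: "each medium packaging contains 5 empty bottles for the first course of treatment and 5 bottles of drugs for the second course of treatment".

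The second course is conditional. Section 4.3, item 8, allows it at week 8 "if the color of treatment area has not subsided completely and there are no serious pigmentation, scarring" or other conditions that the investigator judges unsuitable for re-treatment.

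The analysis is set in two places. Section 14.1 defines the safety set: "Safety population will be defined as all the subjects who received at least one treatment and have actual data of safety indexes". Section 14.5, item 6, tells the analyst to "use listings to describe the AEs and adverse reactions in both groups", includes among the laboratory summaries the "abnormal conversion rate before and after this trial", and ends: "Chi-square test is used for statistical analysis of the adverse reactions". Neither section separates course 1 from course 2, or placebo exposure from hemoporphin exposure.

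**The concern.** Safety is one of the trial's two stated purposes, and course 1 is the only period in which hemoporphin can be compared with placebo. Section 2 confines the primary endpoint to the first stage and, in the same sentence, extends safety to both. Section 14.5(6) then supplies the grouping, a whole-trial laboratory window and the test. An analyst who follows both sections would count reactions to hemoporphin in the column that readers take as placebo.

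That pulls the groups together in relative terms, so a real excess of adverse reactions looks smaller and is less likely to reach significance. For a safety comparison this is the unsafe direction.

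**Working it through.** **Exposure behind the comparison.** In course 1, 0 of 110 controls receive hemoporphin. By the end of course 2, up to 110 of 110 have received it once, and the 330 trial subjects have received it up to twice.

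**Inputs.** The group sizes, 330 and 110, come from section 3.1. The protocol states no adverse reaction rate and no safety power, so it has no figure of its own to reproduce here. The following are assumptions:
- q is the risk of a reaction in a hemoporphin course, and b the risk in a placebo course.
- f_T and f_C are the shares of the trial and control groups treated in course 2.
- Courses are independent, and entry to course 2 is unrelated to reaction risk.
- There is no dropout.

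**Formulas.**
- Course 1 only: trial q, control b, risk ratio q/b.
- Both courses, trial group: T = 1 − (1 − q)(1 − f_T·q).
- Both courses, control group: C = 1 − (1 − b)(1 − f_C·q).
- Power: exact enumeration of the Pearson chi-square test, two-sided 5%, 330 against 110.

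**Worked case, q = 10%, b = 2%.**
- Course 1: 10% against 2%, risk ratio 5.0, difference 8.0 points, power 87%.
- Everyone re-treated: T = 1 − 0.90 × 0.90 = 19.0%; C = 1 − 0.98 × 0.90 = 11.8%. Risk ratio 1.6, difference 7.2 points, power 41%.
- Half the trial group and all controls re-treated: T = 1 − 0.90 × 0.95 = 14.5%; C = 11.8%. Risk ratio 1.2, difference 2.7 points, power 10%.

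The third case matters because re-treatment requires incomplete clearance. If the drug works, controls are likely to be re-treated more often than trial subjects.

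**Range over assumed rates (risk ratio, power).**

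| q / b | Course 1 only | Both, all re-treated | Both, 50% of trial group and all controls |
|---|---|---|---|
| 5% / 1% | 5.0, 46% | 1.6, 21% | 1.2, 6% |
| 10% / 2% | 5.0, 87% | 1.6, 41% | 1.2, 10% |
| 20% / 5% | 4.0, 99% | 1.5, 66% | 1.2, 12% |
| 50% / 10% | 5.0, >99% | 1.4, 97% | 1.1, 29% |

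**Direction.** Expanding the formulas gives T = q + f_T·q(1 − q) and C = b + f_C·q(1 − b). So T/C is below q/b whenever b·f_T(1 − q) < q·f_C(1 − b). With q above b this always holds if controls are re-treated at least as often as the trial group. The direction therefore does not depend on the particular rates, though the size does.

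**What shrinks.** With everyone re-treated the absolute difference is (1 − q)(q − b), here 0.90 × 8 = 7.2 points, so it is nearly kept. The loss is in the risk ratio and in power, because the background rate in both groups has risen. With unequal re-treatment the absolute difference shrinks as well.

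**Course 2 alone.** Entry depends on course 1 clearance and on the absence of serious pigmentation or scarring. A between-group comparison restricted to course 2 would therefore compare groups selected on course 1 outcome. This is a separate issue from the whole-trial comparison.

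**The case against.** The best defence is that no sentence in the protocol pools the two courses into one test. Section 2 states a scope, and including course 2 safety is proper. The chi-square sentence in 14.5(6) names no period. Other places suggest a course-level structure:
- The section 3.1 table describes only course 1 as placebo-controlled.
- Section 6 schedules laboratory tests before each treatment and on Day 4 after it, and adverse event observation in each course.
- Section 9.1 compares laboratory results around the treatment rather than around the trial.
- Section 14 leaves detail to the statistical analysis plan, which could split by course.

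Part of this stands. The pooled comparison comes from reading sections 2 and 14.5(6) together, and section 9.1 makes the laboratory window less than certain. But scope, grouping and test are all fixed here without a split, so this is more than detail left for later. A plan that tested course 1 only would have to narrow what these two sections say when read together.

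A reader might also infer more than the text supports:
- *That the comparison is always two active doses against one.* Course 2 is conditional, so some controls may receive no hemoporphin and some trial subjects only one course.
- *That conditional entry destroys randomisation.* A whole-trial comparison by assigned group is still randomised, between immediate and deferred drug. Selection affects only a comparison within course 2, which the protocol does not specify.
- *That the safety signal would vanish.* This needs the further assumption that susceptible people react at their first active dose, and nothing in the protocol supports it.
- *That the word Randomized in the course 2 row of the section 3.1 table is an error to correct.* Subjects keep their assignment, and the label changes no result.

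**Conclusion.** The concern holds in this form: sections 2 and 14.5(6), read together, set a between-group safety comparison over both courses that is not active against placebo, because controls who enter course 2 receive hemoporphin. It understates the relative excess of adverse reactions as long as hemoporphin carries the higher risk and controls are re-treated at least as often as the trial group.

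The size cannot be derived from the protocol. Under the assumed rates, course 1 risk ratios of 4 to 5 fall to about 1.4 to 1.6 with full re-treatment and to about 1.1 to 1.2 with unequal re-treatment. The loss of power ranges from slight (reactions very common, everyone re-treated) to nearly complete. These figures illustrate and do not predict. The trial was sized on efficacy and a regulatory minimum, so the loss of safety power breaks no stated target. The primary endpoint, which is confined to the first stage, is untouched.

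**What to change.** In sections 2 and 14.5(6), state that the between-group safety test uses course 1 only, up to the second infusion. It should cover adverse events, adverse reactions and laboratory shifts from baseline to Day 4. State that course 2 safety is reported separately and descriptively, by sequence (hemoporphin then hemoporphin, placebo then hemoporphin) and by number of hemoporphin courses received. Replace the whole-trial laboratory window in 14.5(6) with a per-course one, which also brings it into line with section 9.1. The section 3.1 table need not change.

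The cost is a wording change and one extra set of safety tables. Section 6 already schedules adverse event observation and laboratory tests in each course, so no patients, visits or data items are added.

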## 3. Trial design

### 3.1 Design principle:

This is a parallel, placebo-controlled, double-blinded and multicenter clinical trial.

The subjects are randomized into trial group and control group at 3:1 ratio in this phase III clinical trial.

Statistical estimation of the sample size: using two-sided test of the efficacy,  $\alpha=0.05$  and  $\beta=0.1$  (power=90%) based on phase II clinical trial results, the expert panel estimates the total clinical efficacy rate of hemoporphin for injection to be 75.0% in the treatment of port-wine stains and expects a 40% difference from the placebo group; consequently, the estimated minimal number of subjects is 66 for the trial group and 22 for the control group.

In compliance with the SFDA requirement of minimum sample size of no less than 300 subjects for phase III clinical trial group, and also taking into account of dropout, the sample size of this clinical trial was determined to be 330 subjects for the trial group and 110 subjects for the control group, giving a total of 440 subjects.

The subjects will be assigned into trial group or control group by stratified block randomization to receive not more than 2 courses of treatment. The control group receive placebo during the first course of treatment followed by trial drug during the second course of treatment. Each course of treatment will last for 8 weeks. Based on the phase II clinical trial results, the trial drug dose is set at 5mg/kg.

The trial design profile is shown in the following table.

| Trial period                   | Hemoporphin for injection dose | Group and number of cases     | Design principle                                                          |
|--------------------------------|--------------------------------|-------------------------------|---------------------------------------------------------------------------|
| The first course of treatment  | 5mg/kg                         | 330 subjects in trial group   | Randomized, double-blinded, placebo and parallel-controlled (multicenter) |
|                                | 0mg/kg                         | 110 subjects in control group |                                                                           |
| The Second course of treatment | 5mg/kg                         | 330 subjects in trial group   | Randomized, double-blinded (multicenter)                                  |
|                                | 5mg/kg                         | 110 subjects in control group |                                                                           |

